## 8. METHODS

## *8.1. Study parameters/endpoints*

### *8.1.1. Main study parameter/endpoint*

Percentage of patients with curative metastasectomy of liver- and lung metastasis from colorectal carcinoma in the study period: July 2010 – October 2012.

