13. REFERENCES

**1. SUMMARY**

**Title**: Computer supported CEA surveillance after curative treatment of colorectal cancer

**Aim of the study**: The aim of the current study is to develop an evidence-based guideline with standard diagnostic tools (CEA and CT scan) that results in a (cost-) effective recommendation which is applicable for all hospitals in the routine follow-up after curative treatment of colorectal cancer.

**Study design**: In the intervention group follow-up, care consists of bi-monthly CEA measurements starting three months after surgery, a yearly outpatient clinical visit and CT imaging after one and two years. Patients will be closely monitored in an outpatient setting by a frequent testing of CEA, supported by a computer-based system (CEA watch). The patients will be asked to assess their CEA value every 8 weeks. The computer-based system allows us to closely monitor the blood values and to communicate the results to the patient as soon as possible (by e-mail and/or p-mail). In case of two consecutive significant rises in CEA values, extra imaging diagnostics will be performed. In the control group the intervention is follow-up care as usual according to the Dutch national guideline. The starting point of the new regimen will be randomised among the participating clinics.

**Endpoints**: Primary outcome: increase of 15 percent of radical resected metastases in patients as expressed as the percentage of total recurrences. Secondary outcomes: overall survival time cancer specific survival time, time to recurrent disease, quality of life, and costs related to diagnostics.

**Statistics**: Increase in percentage of resected metastases from 10-25% needs 115 patients with metastases in both groups. With an expected recurrence rate of 25%, 460 patients per group are needed. After correction factor about 800 patients per group are needed.

In the economic evaluation costs of both follow-up strategies will be assessed and compared. In addition cost-utility analysis will be conducted based on Quality Adjusted Life Years (QUALY’s).

**Study duration**: The study will be conducted in three years. After a start up period of six months all eligible patients will be identified and registered. Three months later every three months a new pair of hospitals will be randomized to start the new schedule of follow-up and all registered patients will start with the intensive schedule. The last three months will be used for analysis of the data.

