**5. STUDY DESIGN**

This trial is a randomized national multicentre study comparing intensified and conventional follow-up schedule for patients after curative treatment of colorectal cancer. The inclusion is during maximal 2.5 years or until 2000 patients are included. Total expected duration 3 years. Patients may enter during their first three years after curative treatment[[1]](#footnote-2) of colorectal cancer.

The study is constructed with the stepped-wedge design. This implies a randomization at hospital level. The surgeons in a hospital control all their eligible patients according to the care as usual. At the moment determined by the randomization, all included patients will change to the intensified study follow-up protocol. As a result, the early-randomized hospitals have a large amount of patients in the study group and a small amount of patients in the control group, where in the late-randomized hospitals it is the other way around. Randomization will take place on July 1st, 2010 and randomization will be performed per two hospitals. The firstly randomized hospitals start with the intensified follow-up scheme on January 1st, 2011 and since ten hospital will participate, the last two hospitals start with the intensified follow-up scheme at January 1st, 2012.

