*7.2.1.Procedure when CEA crosses the threshold value (see flowchart, addendum 2)*

Increase > 20% in 8 weeks > repetition of CEA measurement in 4 weeks, also measuring CRP level.

Increase in second measurement after 4 weeks > 10%, with a lower static threshold value of 2.5 ng/ml > outpatient clinic visit; if explanation of rise is clear from clinical reasons (ie., active infection): treat infection and re-assess CEA value after 4 weeks. If increase:

-> Evaluation by helical CT Thorax/abdomen within two weeks:

-> Outpatient clinic within 7 days after CT scan

At this visit an assessment is made evaluating

- The presence of resectable metastasis in liver or lung

- Physical signs suggesting other localizations of recurrent disease

- Fitness of the patient to undergo treatment of metastasis

When curable metastases are found and the patient can undergo metastasectomy

-> Treatment at own or referral centre according to the current standard

When irresectable metastases are found or the patient is unfit to undergo metastasectomy

-> Referral to medical oncology for palliative chemotherapy according to the current standard;

-> Referral to radiotherapy when palliative radiation is clinically considered

When no liver and lung metastases are found on CT scan

-> CEA measurement as before

-> Next step dependent on outcome, to discuss in interdisciplinary platform

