# 10.STATISTICAL ANALYSIS

In the clinical study, the main analysis will be based on the differences between care as usual (pre-treatment) and care after implementation of the CEA watch (post-treatment) regarding the percentage of patients with resected metastases, using a multilevel model to adjust for the clustering. For the quality of life data the same analysis will be applied. In addition, potential confounders such as age, gender and tumour status will be considered.

In an economic evaluation, costs and outcomes of both follow-up strategies will be assessed and compared. Research question in the economic evaluation: “What is the incremental cost-effectiveness of a computer based (CEA-watch) follow-up protocol, compared to follow-up care as usual?” Results of the cost-effectiveness analysis will display the additional costs per additional patient with curative metastasectomy. In addition, a cost-utility analysis will be conducted, based on the quality adjusted life years (QALYs). Both types of analyses will be conducted in order to be able to estimate the balance between costs and effects on health, survival and quality of life. Costs will be studied from a societal perspective, during a time period maximally 3 years. Since the time horizon of the study exceeds one year, both costs and effects beyond the first year will be discounted, using various discounting rates of 3%, 4% and 5%, and no discounting, to facilitate international comparison of study results.

Bootstrapping will be performed on the cost and effect pairs in order to calculate confidence intervals. Cost effectiveness acceptability curves will be constructed to illustrate the probability that the different follow-up strategies will be cost-effective, given different monetary values per additional unit of health (patient with patient with curative metastasectomy/QALY).

Relevant cost components of both follow-up strategies will be assessed for all included patients. Main cost categories will be ultrasound, CT-scan, colonoscopy, CEA assay, ‘CEA watch’ system, additional diagnostic tests, outpatient visits, hospital admissions and travel expenses.

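### The primary endpoint window closes in October 2012 with no lag for pending resections and no rule tying a resection to the schedule that detected the recurrence

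*Protocol*

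**What the plan says.** Section 8.1.1 of the protocol sets the main parameter as "Percentage of patients with curative metastasectomy of liver- and lung metastasis from colorectal carcinoma in the study period: July 2010 – October 2012". The Summary (section 1) gives the same outcome with recurrences as denominator: "increase of 15 percent of radical resected metastases in patients as expressed as the percentage of total recurrences". Section 10 bases the main analysis on "differences between care as usual (pre-treatment) and care after implementation of the CEA watch (post-treatment) regarding the percentage of patients with resected metastases". Clustering is handled with a multilevel model.

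On timing, section 5 states: "At the moment determined by the randomization, all included patients will change to the intensified study follow-up protocol". It also states: "The firstly randomized hospitals start with the intensified follow-up scheme on January 1st, 2011". The last of the five pairs starts on 1 January 2012. The Summary spaces the steps three months apart, allows three years in all with six months of start-up, and reserves the last three months for analysis.

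No section says whether a resection belongs to the period of detection or the period of surgery. No section provides for following recurrences that are detected but not yet resected when the window closes. Section 7.2.1 leaves treatment of resectable metastases to the current standard and gives no time to surgery.

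**The concern.** A resection follows detection after some delay, and one calendar cut-off treats the two schedules differently. The last months of the window contain intervention time only. A recurrence found then can enter the denominator before its resection can enter the numerator. Control-detected recurrences do not face this, because the control period has ended everywhere by 1 January 2012.

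The hospital-level switch raises a second question. A patient can be diagnosed under usual care and resected after the hospital has changed. If surgery date decides the period, that resection is credited to the new schedule. What is at stake is the estimated difference in the primary endpoint and the power to detect the planned 15 points.

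**Working it through.** **Plan's own figures.** For 10% v 25%, two-sided 5% and 80% power, the two-proportion formula with continuity correction gives 113 per group (100 without), against the stated 115. Then 115 / 0.25 = 460, and 460 × 1.71 = 786.6, which is the stated figure of about 800. The sample size reproduces and is not in question. Power at 115 v 115, without continuity correction or clustering, is 85%.

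**Window length.** From the Summary, 36 − 6 − 3 = 27 months, which matches July 2010 to the start of October 2012. No time for pending resections is left over.

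**Exposure per hospital** (section 5 dates, three-month steps, two hospitals per step):
- Control months: 6, 9, 12, 15, 18; total 2 × 60 = 120 hospital-months.
- Intervention months to the start of October 2012: 21, 18, 15, 12, 9; total 2 × 75 = 150 hospital-months.
- Counting to the end of October adds one month for each of ten hospitals, giving 160.

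**Assumptions.** Recurrences are the denominator, as in the Summary and section 6.4, and are dated at detection. The detection rate is flat, and the lag L from detection to resection is fixed. L is not in the documents and is shown at 2, 3 and 6 months. Across ten hospitals, L months equal 10L hospital-months.

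**Rule A: detection date decides, resections counted only inside the window.** Control stays at 10%. Intervention = 25% × (150 − 10L) / 150.

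| L (months) | Intervention reads | Difference (points) | Power at 115 v 115 |
|---|---|---|---|
| 0 | 25.0% | 15.0 | 85% |
| 2 | 21.7% | 11.7 | 68% |
| 3 | 20.0% | 10.0 | 57% |
| 6 | 15.0% | 5.0 | 21% |

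Counting to the end of October, with 160 in place of 150, gives 21.9%, 20.3% and 15.6%, with power 69%, 59% and 25%. With no true effect (10% in both) and L = 3, intervention reads 10% × 120 / 150 = 8%.

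**Rule B: surgery date decides, no resections pending at July 2010.** Take L = 3.
- No true effect: control = 10% × (120 − 30) / 120 = 7.5%; intervention = (10% × 120 + 10% × 30) / 150 = 10%. The false gain is 2.5 points.
- Planned effect: control 7.5%; intervention = (25% × 120 + 10% × 30) / 150 = 22.0%. The difference is 14.5 points. Counting to the end of October gives 22.2% and 14.7 points. The planned difference is 15.

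**Rule B with full carry-in.** If resections pending at July 2010 are counted in control at the same rate, control = (10% × 90 + 10% × 30) / 120 = 10%. The false gain disappears. At the planned effect the difference becomes 22.0 − 10.0 = 12.0 points, so the near-cancellation also depends on there being no carry-in.

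**The case against.** The strongest reply is that period-attribution rules are often settled in a statistical analysis plan, which is not at hand. That stands for the dating rule. It does not cover the window, because section 8.1.1 fixes its end and the Summary gives the remaining time to analysis.

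A reader might infer that the percentages are biased both at the switch and at the end. The documents do not support that as an unconditional statement. Under detection dating there is no switch error. Under surgery dating the switch error needs little or no carry-in, and section 6.3 excludes only incurable metastases at study start, so patients awaiting a curative resection are not clearly kept out. The full end loss of Rule A and the false gain of Rule B come from different rules and must not be added.

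A reader might also infer that the direction of the result could be an artefact. With no true effect the two rules do push opposite ways, but no scenario computed at the planned effect reverses the sign. The end loss also works against the intervention, so it is conservative for a claim of superiority.

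Two further inferences fail. The interval from the switch to a first CEA-triggered diagnosis is part of implementing the schedule, and no hospital has fewer than about nine intervention months, so comparing it with one step shows no bias. The inclusion rule ("The inclusion is during maximal 2.5 years or until 2000 patients are included") is a maximum with no stated start date, and patients entering after the window closes would simply add nothing to the endpoint.

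Finally, every magnitude rests on an assumed lag. That is true, and the range is wide, but the direction of the end loss under detection dating holds for any lag above zero.

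**Conclusion.** The point holds in a limited form. The endpoint window has no closing lag, and under detection-date counting this lowers the intervention percentage alone. At an assumed three-month lag, 25% reads as about 20% and uncorrected power falls from 85% to about 57%. Over two to six months the range is 22% to 15%, and 68% to 21%. Under surgery-date counting the comparison is open to bias at the switch: a false gain of up to 2.5 points at three months with no true effect and no carry-in, and a near-cancellation (14.5 to 14.7 against 15 points) at the planned effect.

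These sizes assume flat rates, a fixed lag, recurrences as denominator, and 115 per group without clustering. The change should be made because the loss follows from a stated window and is cheap to avoid. The stated sample size is unaffected.

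**What to change.** In sections 8.1.1 and 10:
- Assign each recurrence and its resection to the schedule in force at first detection, defined as the date of the test or visit that led to the diagnosis.
- Keep detection open to October 2012, giving the exact closing day.
- Count a resection if it takes place within one fixed interval after detection, the same in both periods. The documents give no basis for its length, so the sponsor should justify the choice.
- Collect resections by chart for that interval after October 2012, for recurrences already detected.
- State the denominator in the same sentence, since the Summary uses recurrences and section 8.1.1 uses patients.

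The cost is a primary analysis delayed by the chosen interval and some extra chart collection, with no extra visits. Closing detection early is not a good substitute: six months across ten hospitals would remove 60 of 150 intervention hospital-months (40%) and leave the last pair with 9 − 6 = 3 months.

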### *8.1.2. Secondary study parameters/endpoints*

Calculation of the optimal threshold values and measurement frequency of CEA by

means of calculating ROC curves based on actually measured CEA values.

Percentage of patients that show metastasis on CT thorax/abdomen when the rise of CEA at the chosen threshold values is above normal, and percentage of patients that do not show metastasis on CT thorax/abdomen despite rise of CEA.

Percentage of patients that show metastasis on regular CT Thorax/abdomen with no rise of CEA above normal (false negative rate of CEA measurement)

Overall survival, disease-free survival and recurrence-free survival

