Carcinoembryonic antigen (CEA) is a serum tumor marker used in follow-up of colorectal cancer. It is a protein expressed at the surface of endodermal cells during embryological development, where it has a role in cell-to-cell adhesion. In adults, it is expressed in malignancies and benign inflammatory disease of endodermally derived organs, such as the small and large bowel, pancreas, lung and thyroid. Smoking and other malignancies such as breast and ovarian cancer can increase serum CEA as well. Gold and Freedman discovered it as one of the first serological tumor markers in 1965. Staab developed the basis for it’s clinical application around 1980, after which it was introduced in daily clinical practice for colorectal cancer. The advised frequency of CEA testing in guidelines is ambiguous. The Dutch guideline advices CEA measurements every 3 to 6 months for the first 3 years, and every 6 months in year 4 and 5. The US guideline for CEA advices every 3 months for at least 3 years. Furthermore, no advice is given on the interpretation of CEA results. The key to an effective use of CEA is frequent assessment and an interpretation of test results based on the absolute value as well as on the trend in CEA increases (if present). In this way both sensitivity and specificity of CEA testing may be increased. (Steele, Boey, Staab, [name] (b)). Several authors mention the lack of compliance to frequent CEA measuring, especially in the elderly patient (Cooper). However, in our single-centre trial with intensified CEA measurements, compliance of patients was high. ([name], manuscript in preparation) and major part of the problem might be the doctor’s low compliance to the guidelines. As a result, in daily practice a significantly lower frequency of CEA was generally performed; causing a much less effective result of CEA testing ([name](a), Graham, Steele, Minton, [name] (c), Spratlin). With the availability of a computer support system this problem is mostly solved.

*2.4.* *CEA watch*

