**4. Endpoints**

*4.1. Primary endpoint*

The increased percentage of patients with intended curative metastasectomy of liver- and lung metastases from colorectal carcinoma in the intensified follow-up schedule.

*4.2. Secondary endpoints*

1) Overall survival, disease specific survival, disease free survival

2) Calculation of the optimal threshold values and measurement frequency of CEA

3) The correlation between CEA and helical CT abdomen/thorax: specifically whether the metastasis can be localized when CEA values suggest metastatic disease.

4) Evaluation of the effects of the follow-up protocol: psychological effects and logistic effectuation

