**7. TREATMENT PERIODS**

*7.1. Control period*:

Outpatient clinic at 3 months after end of treatment (surgery or adjuvant chemotherapy)

Assessment for fitness to undergo metastasectomy[[2]](#footnote-3)

Care as usual according to the Dutch guidelines ([www.oncoline.nl](http://www.oncoline.nl/)) and local amendment. The actual care as usual given may differ per hospital. Herefore, the standard care as usual per hospital will be described.

Filling out the questionnaire “SF-12 “ after 12 months

*7.2. Intervention period*:

Outpatient clinic at 3 months after end of treatment (surgery or adjuvant chemotherapy)

Assessment for fitness to undergo metastasectomy2

During year 1

CEA measurement every 8 weeksatlocal laboratory, report results by letter. The possibilities for blood sampling at a local laboratory are now examinated per hospital. The measurement will take place at the hospital itself, samples will be mailed to the laboratory.

If no special events occur, no additional out patient clinic visits

At year 1 helical CT-abdomen[[3]](#footnote-4) and colonoscopy[[4]](#footnote-5)

Filling out the questionnaire “SF-12 “ after 12 months

Filling out the questionnaire of intensified follow-up at 1 year

One year after surgery outpatient clinic visit

- Results from evaluation (CT) and evaluation long term surgical results

- Update assessment for fitness metastasectomy

During year 2

CEA measurement every 8 weeks atlocal laboratory, report results by letter

If no special events occur, no additional out patient clinic visits

At year 2 helical CT thorax/abdomen4

Two years after surgery outpatient clinic visit

Results from evaluation (CT) and evaluation long term surgical results

Update assessment for fitness metastasectomy

During year 3

CEA measurement every 12 weeks atlocal laboratory, report results by letter

If no special events occur, no additional out patient clinic visits

At year 3 helical CT thorax/abdomen

Three years after surgery outpatient clinic visit

Results from evaluation (CT) and evaluation long term surgical results

Update assessment for fitness metastasectomy

All patients will be informed about the laboratory results by letter or email. In case of positive results patients will be invited to undergo a CT scan followed by an outpatient clinic visit. All patients will have access to the surgeon’s outpatient clinic in case of questions or clinical complaints.

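### ROC curves can inform the CEA threshold but do not by themselves yield a measurement frequency, and the design never varies the interval on its own

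*Protocol*

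**What the plan says.** Section 4.2 lists as a secondary endpoint: "Calculation of the optimal threshold values and measurement frequency of CEA". Section 8.1.2 repeats it and gives one method for both quantities, namely by "means of calculating ROC curves based on actually measured CEA values".

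The intervals that will produce those values are these:

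- **Intervention (section 7.2):** 8 weeks in years 1 and 2; in year 3, "CEA measurement every 12 weeks". The Summary and the study procedures in section 8 mention only an 8-week or two-monthly interval. These passages should be reconciled; section 7.2 is used here because it is the most detailed.
- **After a rise (section 7.2.1):** "Increase > 20% in 8 weeks > repetition of CEA measurement in 4 weeks, also measuring CRP level". A second rise above 10%, with a floor of 2.5 ng/ml, leads to a clinic visit and on towards CT.
- **Control (sections 2.3 and 7.1):** usual care under the national guideline with local variation between hospitals. On the guideline, section 2.3 states: "The Dutch guideline advices CEA measurements every 3 to 6 months for the first 3 years".

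Section 5 randomises the date on which each pair of hospitals switches from usual care to the whole intensified programme. The first pair switches on 1 January 2011 and the last on 1 January 2012.

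**The concern.** The endpoint asks two questions and the stated method addresses one. Varying the threshold along a ROC curve shows the trade between sensitivity and specificity for a test applied on a given schedule. How often to test is a different choice: later detection is weighed against more tests and more false alarms over time. Neither quantity appears on the curve.

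The study aims at a follow-up guideline, and section 2.3 criticises existing guidelines for ambiguous advice on frequency and for silence on interpretation. This endpoint addresses that gap directly. A frequency recommendation drawn from ROC curves alone, or from comparing the intervals that happen to occur in the data, could reflect years since surgery, hospital habits or the other parts of the programme rather than the interval.

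**Working it through.** The protocol gives no figure for this endpoint, so there is none to reproduce. The check has four steps.

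**1. What the curve leaves out.** Suppose two schedules have the same false-positive rate f per test. False alarms per patient-year are then f × 52/w for an interval of w weeks:

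- 8 weeks: 52/8 = 6.5, so 6.5f
- 12 weeks: 52/12 = 4.3, so 4.3f
- 16 weeks: 52/16 = 3.25, so 3.25f
- 24 weeks: 52/24 = 2.2, so 2.2f

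The same point on a per-test ROC curve thus means twice as many false alarms at 8 weeks as at 16. Delay works the other way. If CEA becomes detectably raised at a random moment between tests (an assumption), the mean wait for the next test is w/2: 4, 8 and 12 weeks at intervals of 8, 16 and 24. Neither the factor of two nor the wait can be read from the curve.

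**2. Which interval contrasts the data contain.**

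| Contrast | What changes with it |
|---|---|
| 8 v 12 weeks, intervention | Coincides with follow-up years 1-2 v year 3 (7.2) |
| 4-week repeats | Taken only after a rise above 20% (7.2.1), so they depend on the outcome |
| Control v intervention | CT schedule, interpretation rule, reminders and visits also change (Summary, 2.4, 7.1, 7.2, 7.2.1) |
| Between control hospitals | Hospital (7.1) |

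No row isolates the interval.

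**3. Whether control and intervention overlap in time.** The Summary gives three-monthly steps and section 5 gives ten hospitals in pairs. Counted from July 2010, the pairs switch after 6, 9, 12, 15 and 18 months.

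- Control hospital-months in total: 2 × (6 + 9 + 12 + 15 + 18) = 120.
- Control during 2011: 2 × (0 + 3 + 6 + 9 + 12) = 60.
- Intervention during 2011: 2 × (12 + 9 + 6 + 3 + 0) = 60.
- Intervention in total to October 2012: 27 × 10 − 120 = 150, or 28 × 10 − 120 = 160 if October is counted.

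Half of control time (60/120) and 38-40% of intervention time (60/160 to 60/150) is concurrent. Patients may enter during the first three years after treatment, and the guideline interval quoted above also covers years 1-3, so both conditions can be observed at the same follow-up year. The obstacle in this contrast is that several components change together, not calendar time.

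**4. How a percentage rise depends on its interval.** The rule in section 7.2.1 begins with "Increase > 20% in 8 weeks". At constant exponential growth the equivalent rise over w weeks is 1.2^(w/8) − 1:

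- 4 weeks: 1.2^0.5 − 1 = 9.5%
- 12 weeks: 1.2^1.5 − 1 = 31%
- 16 weeks: 1.2^2 − 1 = 44%
- 24 weeks: 1.2^3 − 1 = 73%
- 26 weeks (6 months): 1.2^3.25 − 1 = 81%

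The implied doubling time is 8 × ln 2 / ln 1.2 = 30.4 weeks throughout. A ROC curve for relative rise therefore describes the interval that produced it. An analysis across intervals has to be done per interval or on log-CEA change per week.

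**The case against.** The strongest defence is that the sentence in section 8.1.2 is short and can be read generously. A thinned 8-week series still consists of values that were actually measured, so drawing one ROC curve per interval would fit the text. The log scale, thinning and correction for optimism are details that an analysis plan, not shown here, could supply. Section 2.6 describes an earlier phase II study of CEA frequency and interpretation that shaped the flowchart, so the guideline would not rest on this endpoint alone. Much of this stands. It does not remove the mismatch, because even one curve per interval has no measure of delay or of false alarms over time, and the protocol itself ties frequency to that method.

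A reader might infer four stronger things that the documents do not support:

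- **That CEA is measured at only one interval.** Sections 2.3, 7.2 and 7.2.1 give 4, 8 and 12 weeks and 3 to 6 months.
- **That the interval groups share no calendar time or follow-up year.** This is wrong for control versus intervention, as step 3 of the working shows. Only 8 versus 12 weeks coincides with follow-up year.
- **That intervals will be pooled under one percentage, or that accuracy will be reported without correction and so overstated.** The protocol says neither. Section 7.2.1 attaches its 20% to 8 weeks, and its 10% at the 4-week repeat lies close to the 9.5% implied by constant growth.
- **That the data can say nothing about frequency.** Thinning can inform intervals longer than 8 weeks, within limits.

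**Conclusion.** The point holds in a limited form. The protocol names a secondary endpoint on optimal frequency and fixes a method that does not by itself deliver one. The mismatch lies in the stated method; it is not a detail left to an analysis plan. The design does not make up for it, since the interval always changes together with follow-up year, a preceding rise, hospital or the rest of the programme.

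No numerical bias can be given, because the protocol reports no frequency result or accuracy figures. The 31% and 81% equivalents rest on constant exponential growth and show only that threshold and interval must be handled together. The overlap count assumes equal three-monthly steps. The interval contrast takes section 7.2 as the operative schedule.

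The consequence is confined to this secondary endpoint and to any frequency recommendation drawn from it. The primary comparison and the sample size do not depend on it. The text should be amended because the change is cheap and the endpoint bears on the study's guideline aim.

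**What to change.** Amend section 8.1.2, and 4.2 to match, as follows.

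1. **Threshold.** Keep the ROC curves, drawn per measurement interval or on log-CEA change per week, with a patient-level bootstrap to correct for choosing and judging the threshold on the same patients.
2. **Frequency.** Thin the 8-week series within the same patients to 16 and 24 weeks. Both lie inside the guideline's range of 3 to 6 months (about 13 to 26 weeks). For each interval and threshold, report sensitivity, false alarms per patient-year and detection delay relative to 8 weeks.
3. **Limits to state.** Intervals shorter than 8 weeks cannot be judged this way. The comparison is also partly biased, because the 8-week rule itself triggers CT and treatment: what a sparser schedule would have found later is then not observed.
4. **Alternative.** If this analysis is not wanted, restrict the endpoint to thresholds.

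This is an analysis proposal on values collected under the existing schedule and changes nothing in patient care. It costs some added analysis work and a more modest conclusion on frequency.
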